## ***Patients and methods***

### **Study sample**

The study sample will be composed of 1800 patients, evenly distributed over the three study arms. Sample size is based on an expected response rate (for the questionnaire) of 75%. We will include patients who undergo surgery or biopsy (1600 patients) or blood drawing (200 patients). The former category of patients will contain patients who have a skin condition, a colorectal condition or a condition in the head/neck area. We include patients with malignant and non-malignant conditions of the same tissues or organs with a ratio of about 3:2, dependent on availability in each hospital. The absolute number of patients with specific conditions will also depend on the availability of these patients in the four hospitals. In the VUmc we will not include patients with (malignant and benign) colorectal conditions and malignant head/neck conditions, because almost all of them will also be asked to participate in a biobank (String of Pearls Initiative), which might confuse patients about what they are asked to give consent for. In the NKI-AVL, only patients with malignant conditions will be included. Figure 1 gives an overview of the number of patients in each of the groups in the four hospitals.

We will include patients between the ages of 18 and 80 years. There are two reasons for the upper age limit. First, we have learned from experience that patients over 80 are much less likely to be able or willing to complete questionnaires. Second, and more importantly, the two community hospitals in our study treat more patients over 80 than the two academic hospitals. Including these patients would mean that it would be difficult to determine whether any differences observed between patients from these different types of hospitals should be attributed to age differences or other causes.

Patients should be able to speak and read Dutch and have a sufficient mental capacity to complete the questionnaires by themselves. Patients will be included in the study by their treating physician or nurse practitioner.

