### ***Sample size, statistical power***

Sample size is based on an expected response of 75%, allowing sufficient power to address the major outcomes, i.e. consent rates and preferences for procedures, in different subgroups of e.g. hospitals, age and gender. In order to test the hypothesis that the two interventions result in a difference of at least 10% in consent rates, 0.1% non-consent in the opt-out plus or opt-out group versus 10% in the informed consent group, 121 patients per group are needed (80% power and a 2-sided alpha of 0.05; with continuity correction). The difference of 10% is based on our earlier research and the difference is considered a relevant loss of patient materials for research which may lead to selection bias. Because the setting of diagnosis and treatment is different between surgical and outpatient settings and also between general and academic hospitals, it is important to be able to compare the responses in these subgroups. We have also shown in our earlier studies that educational level is associated with preference for a certain procedure and this may also drive response rates of patients. Therefore we propose to include in each intervention group up to 600 patients to be able to conduct subgroup analysis and include adjustment factors; with a response rate of 75% and hence with 450 participants per group we could stratify for 3 to 4 factors, i.e. 90-150 per subgroup, and still have enough power to investigate a difference in response rate of 0.1% versus 10%. Patients will not be stratified by education or sex; we expect these two factors to be equally distributed across groups.

Another reason to obtain a large sample size is that the percentage of non-consenters is small, while it is important to assess their opinions and reasons for non-consent. In the earlier intervention study, 4.6% of respondents indicated in the questionnaire that they wanted to withhold consent or that they did not know whether they wanted to. A sample size of 1800 patients and a response rate of 75% will lead to approximately 62 patients who want to withhold consent or are not sure which choice to make.

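### The stated 90-150 respondents per arm per subgroup corresponds to three to five subgroups, not to stratification by three to four factors, and its lower end is below the protocol's own required 121

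*Protocol*

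**What the plan says.** All of this stands in the Protocol, mainly under Sample size, statistical power.

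- The planning contrast is "0.1% non-consent in the opt-out plus or opt-out group versus 10% in the informed consent group". For it, "121 patients per group are needed (80% power and a 2-sided alpha of 0.05; with continuity correction").
- The arms are then made much larger than that: "we propose to include in each intervention group up to 600 patients to be able to conduct subgroup analysis and include adjustment factors".
- The step from arm size to subgroup size runs "with a response rate of 75% and hence with 450 participants per group" and then "we could stratify for 3 to 4 factors, i.e. 90-150 per subgroup". The section concludes that the trial would "still have enough power to investigate a difference in response rate of 0.1% versus 10" per cent. I read the response rate in that phrase as the consent contrast, because the two percentages are the same.
- Study sample says that the patients are "evenly distributed over the three study arms".

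The number of levels per factor is not given. Nor does the section say whether factors would be crossed or examined one at a time.

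**The concern.** The sentence derives a subgroup size from a number of factors, and a power statement from that subgroup size. The first step does not work. When several factors define strata together, their levels multiply, so three or four factors give at least 8 or 16 cells. A range of 90-150 out of 450 implies only three to five groups.

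This matters because the sentence is one of the stated grounds for 600 patients per arm, and it tells the reader how far the data can be subdivided. If the trial team later reports consent rates within strata formed by several factors, a finding of no difference could be taken as adequately powered on the strength of this sentence when it is not.

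**Working it through.** **Inputs (Protocol, Sample size, statistical power; Study sample).** 600 per arm; 75% response, so 600 × 0.75 = 450; three equal arms; non-consent p1 = 0.001 and p2 = 0.10; two-sided alpha 0.05. Assumption, not in the protocol: where factors are crossed, each has two levels and the cells are equal. More levels would make the average cell smaller.

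**Step 1. Where 90-150 comes from.**
- 450/3 = 150
- 450/4 = 112.5
- 450/5 = 90

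The range is reproduced by three to five subgroups. Dividing by three to four gives only 112-150, so the 90 does not follow even if one divides by the number of factors. Two crossed binary factors also fall inside the range (450/4 = 112).

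**Step 2. Cell sizes if three to four binary factors are crossed.**
- 450/2³ = 56.3 and 450/2⁴ = 28.1 respondents per arm
- 600/2³ = 75 and 600/2⁴ = 37.5 if consent status is known for everyone randomised

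**Step 3. Power formula.** With d = |p1 − p2| = 0.099 and p̄ = (p1 + p2)/2 = 0.0505, uncorrected power at m per group is

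Φ( [d√m − 1.96 √(2p̄(1 − p̄))] / √(p1(1 − p1) + p2(1 − p2)) ).

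For the continuity correction, m is the solution of n = (m/4)(1 + √(1 + 4/(m d)))² for the actual n per group. Example: n = 56 gives m = 37.6 and power 50%. Fisher power is by enumeration of both binomial distributions.

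**Step 4. Power for 0.1% versus 10%.**

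| Per arm | Arises from | Corrected | Uncorrected | Fisher |
|---|---|---|---|---|
| 28 | 450, four crossed binary factors | 18% | 39% | 5% |
| 37 | 600, four crossed binary factors | 29% | 49% | 16% |
| 56 | 450, three crossed binary factors | 50% | 67% | 48% |
| 75 | 600, three crossed binary factors | 67% | 80% | 75% |
| 90 | 450, five subgroups | 77% | 86% | 88% |
| 112 | 450, four subgroups | 87% | 93% | 96% |
| 150 | 450, three subgroups | 96% | 98% | >99% |

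The protocol specifies the corrected calculation. On it, no cell from three or four crossed factors reaches 80%.

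**Step 5. The 90 against the required number.** The section requires 121 per group, so a subgroup of 90 fails its own criterion on any reading of the factors. The 121 is itself not what its inputs give: 0.1% versus 10% at 80% power needs 95 per group with the correction and 76 without. A figure of 121 results from 1% versus 10% at 80%, or from 0.1% versus 10% at 90%, both corrected. That is a separate matter. Here it is enough that 28 and 56 lie below 76, 95 and 121, and that 90 lies below both corrected figures.

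**The case against.** The best defence is that factors were meant one at a time. The protocol never says that they are crossed. The section names its subgroups singly (surgical or outpatient setting, general or academic hospital), and Study objectives and Basic plan of analysis also list characteristics one by one. On that reading the stated sizes carry most of the claimed power, 77% to 96% corrected, and an evenly split binary factor would leave 450/2 = 225 per arm. No crossed-cell analysis is set out: the plan compares whole arms and uses covariates in multivariable models if the groups differ at baseline. Such adjusted whole-arm analyses keep nearly full power at 450 per arm. The subgroup sentence is also not the only ground for the sample size. The section cites the need for enough non-consenters (about 62 who would withhold consent or are unsure) and uses 450 per arm for the preference and satisfaction hypotheses.

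Most of this stands. A reader might infer that the protocol commits itself to cells of 28-56, or that the power it claims simply does not exist. The document supports neither, because crossing is an assumption.

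The defence does not rescue the sentence. Taken one at a time, any number of factors could be examined, so a limit of three to four makes little sense. The 90 needs five levels and falls short of 121. Nor are real subgroups equal: Study sample allots 200 of 1800 patients to blood drawing. If these are evenly split over the arms, that is about 67 per arm and 50 respondents, with 44% corrected power (Fisher 37%), or 61% (Fisher 65%) if all 67 count.

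**Conclusion.** The sentence is wrong as written. The figure 90-150 belongs to three to five roughly equal subgroups, and the claim of enough power does not carry over to stratification by three to four factors.

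The size of the problem depends on a reading that the protocol leaves open:
- Crossed: at most about 56 to 28 respondents per arm per cell on average, and corrected power of about 50% to 18%. If consent status is known for all 600 per arm, it is about 67% to 29%. This rests on equal binary factors.
- One at a time: about 77% to 96%, with a lower limit that contradicts the required 121.

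It would go too far to conclude that the trial is too small for its consent hypothesis. At 450 per arm the whole-arm comparison of 0.1% with 10% has power close to 100%. What is affected is the stated capacity for subgroup analysis.

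**What to change.** Replace the sentence with wording such as: three to five roughly equal subgroups (one factor at a time, or two crossed binary factors) leave about 90-150 respondents per arm per subgroup, with about 77-96% continuity-corrected power for 0.1% versus 10%; crossing three to four factors leaves at most about 28-56 respondents per cell on average and is not powered.

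Drop the claim of enough power for stratification by three to four factors. Reconcile the lower limit of 90 with the 121 per group required in the same section, after checking the 121 against its inputs. If consent status will be available for all 600 per arm, say so and give the corresponding cell sizes (75 and 37) and power.

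The cost is a small text change in one section. The stated subgroup capacity becomes more modest. Enrolment and the main whole-arm comparison stay as they are.

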## **Outcomes**

The primary study outcomes will be used to determine which consent procedure serves the needs of patients, clinicians and scientific research best. If one of the three consent procedures serves the needs of all three of these parties best, we will conclude that this consent procedure is the best candidate to become the standard procedure in the Netherlands that prescribes whether and how patients should be asked consent for the use of residual tissue. If the needs of these three parties are best served by different consent procedures, or if it is unclear which consent procedure serves the needs of one or more of the parties best, we will organize an invitational conference in which we invite different stakeholders, such as clinicians, patient organizations and researchers, to discuss how to translate our research findings into clinical practice.

Which consent procedure serves a party's needs best will be decided along the following lines:

- For patients: satisfaction with the received information in the 'best procedure' should be significantly higher than in the consent procedure with the lowest satisfaction rates. Further, the consent procedure should have the highest preference rates among respondents, with a minimum of a 10% difference with the consent procedure with the lowest preference rate. Additionally, the proportion of patients aware of storage of tissue and research use should be at least as high as in the other two groups.

- For clinicians: satisfaction with the received information in the ‘best procedure’ should be significantly higher than in the consent procedure with the lowest satisfaction rates. Further, the consent procedure should have the highest preference rates among participating clinicians and nurse practitioners, with a minimum of a 10% difference with the consent procedure with the lowest preference rate. Additionally, more than 75% of the responding medical staff should indicate that the consent procedure ‘never’ or ‘seldom’ interferes with giving clinical information.
- For research: consent rates for the procedure for which patients and/or clinicians have the highest preference should be at least as high as consent rates in the two other procedures.

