### **Data collection: questionnaires for the medical staff**

The opinions of the medical staff (treating physicians and nurse practitioners) about the different consent procedures and the associated workload will be evaluated by a brief, structured questionnaire administered before and after the interventions.

The pre-intervention questionnaire (see attachment D) consists of:

- Questions about the current situation regarding asking consent for residual tissue use. These questions have been developed for this study.
- Questions to assess which consent procedure clinicians and nurses prefer and their views on the potential drawbacks and advantages (time pressure, properly informed patients) of each of the consent procedures. These questions have been developed for this study.

The post-intervention questionnaire (see attachment E) consists of:

- Questions about how members of the medical staff experienced the three consent procedures with respect to e.g. time pressure and administrative loads. These questions have been developed for this study.
- Questions about how consent procedures in which patients are actively informed about residual tissue use could best be implemented into clinical practice (e.g. timing of the information and who would be able to inform patients). These questions have been developed for this study.

All questionnaires in this study will be tested in a small pilot study. Minor modifications may be implemented based on the results of these studies.

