A sample size of 450 (based on a conservative estimate of a response rate of 75%) will suffice to test the hypothesis that patients prefer the opt-out plus procedure over the informed consent procedure by a difference of at least 10%, based on the difference found in our earlier studies, i.e. 43% versus 34% (75% power and a 2-sided alpha; with continuity correction). In addition, the sample size will be sufficient to test the hypothesis that patients in the opt-out plus procedure are more satisfied with the procedure they are subjected to than patients in the informed consent procedure. In our earlier research 82% of the patients in the informed consent procedure compared with 65% in opt-out plus procedure indicated that they were satisfied with the procedure.

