## ***Basic plan of analysis***

Analysis will first be performed to evaluate the comparability of the intervention groups and the control group at study entry in terms of sociodemographic and clinical characteristics. Student's t-test or appropriate non-parametric statistics will be used, depending on the level of measurement. If the groups are found not to be comparable on one or more background variables, those variables will be employed routinely as covariates in subsequent analyses using multivariate models, such as logistic regression.

The proportion of the outcomes in each intervention arm, i.e. consent rates and patients' satisfaction with and preference for a consent procedure, the proportion of patients aware of storage of tissue and research use, and the satisfaction with and preference for a consent procedure of the medical staff, will be evaluated by comparison of the informed consent

versus the opt-out plus group, and the opt-out plus versus the opt-out group by non-parametric or parametric tests as appropriate. Patient characteristics, satisfaction with and preferences for the information and consent procedures will be evaluated according to patient characteristics such as age, educational level, sex, hospital type, type of clinical procedure, and disease type. All analyses will be performed using SPSS.

A qualitative analysis of the information needs and appreciation of the patients for the consent procedures will be evaluated through questions in the questionnaire and telephone interviews with a representative group of patients who completed the questionnaire.

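### The 75% power for preferring opt-out plus over informed consent is a two-group figure for what is most likely one sample's choice, and the planned between-arm comparison does not test that preference

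*Protocol*

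**What the plan says.** Under Sample size, statistical power, the protocol gives a power statement for patient preference. The claim to be shown is "patients prefer the opt-out plus procedure over the informed consent procedure by a difference of at least 10" per cent, and the protocol regards its sample as adequate for this: "A sample size of 450 (based on a conservative estimate of a response rate of 75%) will suffice to test the hypothesis". The planning values are "based on the difference found in our earlier studies, i.e. 43% versus 34% (75% power and a 2-sided alpha; with continuity correction". The same section shows that 450 is the number per arm: "with a response rate of 75% and hence with 450 participants per group".

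Hypothesis 2 is a ranking: opt-out plus preferred by most patients, opt-out by the fewest. The decision rule under Outcomes says "the consent procedure should have the highest preference rates among respondents", with a margin of at least 10% over the least preferred procedure. Preliminary results likewise reports earlier patients' preference for opt-out plus over the other two procedures.

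Basic plan of analysis evaluates all outcomes, including preference, as proportions per arm. It compares the informed consent group with the opt-out plus group, and the opt-out plus group with the opt-out group. Staff are included: "and the satisfaction with and preference for a consent procedure of the medical staff, will be evaluated by comparison of the informed consent" group and the others. Yet the post-intervention staff form contains "Questions about how members of the medical staff experienced the three consent procedures", and Study design including study arms randomises patients, with one envelope per patient used in randomisation order by the clinician.

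**The concern.** If each respondent names one preferred procedure, 43% and 34% are two shares of the same sample. Their difference has a different variance from that of two proportions in separate groups, so power computed for separate groups does not apply to it.

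The planned contrast also answers another question. Comparing the share preferring opt-out plus in one arm with that in another shows whether experiencing a procedure shifts preference. It could be null while opt-out plus is clearly the favourite, or clear while it is not.

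For staff the contrast cannot be carried out as written. The same clinicians deliver all three procedures, so there is no informed consent group of staff to set against an opt-out plus group. Patient and staff preference are both primary outcomes and feed a recommendation for a national standard procedure.

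**Working it through.** **Inputs.** p1 = 0.43, p2 = 0.34, n = 450 per arm (Sample size, statistical power); three equal arms, so 3 × 450 = 1350 respondents. The preference sentence says two-sided but gives no alpha; 0.05 is assumed from the consent-rate calculation in the same section. Difference d = 0.43 − 0.34 = 0.09, that is, 9 points.

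**1. The plan's own figure: two independent groups of 450.**
- Mean proportion 0.385. Null SE = √(2 × 0.385 × 0.615 / 450) = 0.0324.
- Alternative SE = √((0.43 × 0.57 + 0.34 × 0.66) / 450) = 0.0323.
- Uncorrected power = Φ((0.09 − 1.96 × 0.0324) / 0.0323) = 79.3%.
- With continuity correction, 77.3% (exact enumeration of the Yates or Fisher test: 77.5%). For 75% power, 427 per arm are needed with correction and 405 without.

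The stated 75% is close to this model and slightly conservative. A true 10-point difference (44% vs 34%, or 43% vs 33%) would give about 85% to 86% with correction, so the figure belongs to 9 points, not to at least 10.

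**2. Two shares of one sample of N respondents.**
- Variance of the difference = (p1 + p2 − d²)/N = (0.77 − 0.0081)/N = 0.7619/N.
- Power = Φ((d√N − 1.96√(p1 + p2)) / √(p1 + p2 − d²)).

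| Respondents used | SE | Power | With continuity correction |
|---|---|---|---|
| 450 (one arm) | 0.0411 | 58.6% | 56.5% |
| 900 (two arms) | 0.0291 | 86.9% | 86.1% |
| 1350 (all arms) | 0.0238 | 96.5% | 96.3% |

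For N = 1350: (0.09 × 36.742 − 1.96 × 0.8775) / 0.8729 = 1.818, and Φ(1.818) = 96.5%. Simulation with shares 0.43/0.34/0.23 gives 58.6% at 450 and 96.5% at 1350. The sample for 75% power is 658 respondents, and for 80% it is 744. The stated 75% matches none of the three rows.

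**3. What the between-arm contrast tests.** Suppose every arm splits 43/34/23. Hypothesis 2 then holds exactly. The between-arm difference in the share preferring opt-out plus is 0.43 − 0.43 = 0, so the planned test rejects only at its nominal rate of about 5%, whatever the sample size.

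**4. Staff.** Set side by side, the design section randomises patients, the staff questionnaire covers all three procedures for each staff member, and the analysis section compares groups. The decision rule for clinicians also requires satisfaction significantly above that of the lowest-rated procedure, so a valid staff test is needed.

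**The case against.** The best defence is that the decision does not depend on the criticised test. Hypotheses 1 and 3 speak of significance and hypothesis 2 does not. The decision rule judges preference numerically, against the least preferred procedure. This stands: a reader might infer that the preference ranking is not assessed at all, and that would be wrong. But the sample size section says outright that the sample serves to test opt-out plus over informed consent, and no planned comparison does so.

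A reader might also infer that standard errors for patient preference will be wrong. The documents do not support that. Randomised arms are independent, so the between-arm standard error is right for its own contrast; the fault lies in the question it answers.

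Nor does the 59% show a trial that is too small. It applies only if one arm's respondents are used, and the preference questions appear in the questionnaire sent to all recruited patients.

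The form of the preference question is inferred, because attachment B is not shown. If patients rated each procedure separately, or could give several answers, the variance formula and exact powers would change. This stands as an assumption.

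For staff, the protocol states no power, so none can be called wrong. How far an unpaired analysis would misstate the variance depends on a within-person correlation that the documents do not give. Leaving tests to be chosen as appropriate does leave the method open, but the contrast is fixed as group against group.

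Finally, whether exposure shapes preference is a legitimate question. It deserves a place, but not as the test of hypothesis 2.

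**Conclusion.** The concern holds in a limited form. The 75% power approximates a two-independent-group calculation (77% to 79% at 450 per arm) and does not describe a comparison of two shares among the same respondents, which has 58.6% power with 450 and 96.5% with 1350. The planned between-arm comparison does not test whether opt-out plus is preferred over informed consent, so the hypothesis stated in the power paragraph has no valid formal test. The staff comparison presumes groups that the design does not create.

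This rests on a single-choice preference item (inferred from Preliminary results, Hypotheses and Outcomes), a two-sided alpha of 0.05, and shares of 43% and 34% that hold across arms. The defect is in the stated method and power figure: with all respondents pooled, the planned sample is ample. Patient satisfaction with the procedure received is properly a between-arm outcome and is unaffected. The gap between 9 points and at least 10 is a small wording error.

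**What to change.** - **Patient preference, main analysis:** estimate the shares in all respondents pooled over the three arms. Test opt-out plus minus informed consent within respondents, with variance (p1 + p2 − d²)/n or a binomial test among those choosing either procedure.
- **By arm:** report preference in each arm, and keep the between-arm comparison as a secondary question about the effect of exposure.
- **Power paragraph:** state about 96% to 97% for 43% versus 34% with 1350 respondents, say that this assumes the shares hold across arms, give the alpha, and call the difference 9 points.
- **Preference item:** state whether respondents make one choice; if not, adapt the variance.
- **Staff:** compare satisfaction and preference within person, not between groups.

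The cost is rewording of the power and analysis sections, with no extra patients or data. One small downside is that the pooled estimate averages preference over the trial's 1:1:1 mix of exposures, which is why the results by arm should stand beside it.
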